#### End-of-trial analyses

The total blood collected by 2 years will be expressed in units (470 ml) per person per year. Means will be compared between groups using a t-test, with subsidiary analyses of covariance adjusting for baseline characteristics. The mean differences between groups in the PCS of the SF-36v2 will be adjusted for baseline PCS by analysis of covariance, and in secondary analyses for other baseline characteristics. Possible bias from missing data will be investigated by multiple imputation within each randomised group based on sequential additions to the imputation model: (1) baseline characteristics, (2) interim SF-12v2 scores, (3) deferral at previous blood collections, (4) number of blood collections made, and (5) number of reminders to elicit web questionnaire responses [33–35]. Other secondary outcomes will be analysed similarly. The proportion of deferrals will be analysed using logistic regression, allowing for potential over-dispersion between individuals. The baseline predictors (including genetic characteristics) of levels of haemoglobin and ferritin, and rates of deferral will be investigated using multiple (logistic) regression, employing cross-validation techniques to prevent over-fitting [36].

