### Randomisation, concealment of allocation, and blinding

Randomisation to three sex-specific intervention groups in the ratio 1:1:1 was undertaken at the academic trial coordinating centre using individual-level randomisation achieved by means of a computer programme built into the trial database. This programme includes a minimisation algorithm to ensure that key prognostic characteristics are balanced across the trial arms at baseline (for example, new/repeat donor status, weight and age, as shown in Table 2). Randomisation was stratified by donation centre and gender. By the nature of the trial, participants have not been blinded to the intervention group to which they have been allocated.

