### Baseline data collection

On the day following enrolment into the study, NHSBT confidentially retrieved data on participants from donor records, including donor number, donation number, donation date, email and mobile contact details, sex, month and year of birth, NHS number and previous donation and deferral history in the past 5 years. Using secure systems, these data were transferred to the academic coordinating centre to facilitate contact of participants, implementation of trial protocols, tracking of participants’ appointments and attendances throughout the trial. A few days after joining the trial, participants received two emails: one containing a uniform resource locator (URL) link and requesting completion of the trial’s baseline questionnaire, and another containing a password to access the online questionnaire. Participants’ trial IDs were embedded within the URL link using a custom tag to anonymously track completion of the questionnaire. Participants were requested to complete the questionnaire within 7 days and received two email reminders and a phone call between days 7 and 14 if they did not respond. The baseline questionnaire has been designed to take approximately 15 minutes to complete and includes the following:Compulsory questions including month and year of birth, sex, height, and weight. This information was used to verify that the questionnaire had been completed by the individual to whom it was sent, and also for minimisation algorithm described above.Quality of life questions, using the Short Form Health Survey (SF-36v2) questionnaire. The SF-36v2 is a generic measure of health status that has been reported to differentiate well between health benefits produced by a range of treatments irrespective of age, disease condition, or treatment group [17–20]. It is composed of 36 questions and produces an eight-scale profile of functional health and well-being, as well as two psychometrically-based summary measures (that is a physical component score (PCS) and mental component score) and a preference-based health utility index.Previous history of iron deficiency, which may relate to susceptibility to iron deficiency.Brief lifestyle information including, diet (particularly related to iron intake and absorption), alcohol intake, smoking and physical activity.

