### Outcome measures

#### Primary outcome

The primary outcome is the number of blood donations made over 2 years. The number of blood donations up to (and not including) the 2-year anniversary date of recruitment will be counted.

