### Data analysis

#### Principles

Intention-to-treat analyses will be used, comparing groups as randomised. Results for men and women will be analysed separately. The principal pair-wise comparisons of groups for men will be between 10-wk and 12-wk, and between 8-wk and 12-wk intervals. For women, these comparisons will be between 14-wk and 16-wk, and between 12-wk and 16-wk intervals. For outcomes assessed at both baseline and at the 2-year follow-up, analyses of the 2-year follow-up measures will be adjusted for the baseline measures. Other baseline characteristics (age, centre, BMI and weight, SF-36v2 physical and mental component scores, haemoglobin and ferritin) will be adjusted for in secondary analyses. Tests of interaction will assess whether results differ between the subgroups pre-specified above. Multiple testing will be taken into account when interpreting these results. The trial will be reported according to CONSORT guidelines.

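### The primary t-test on donations ignores the factors used in allocation and the donation history already held; it is valid but somewhat conservative and less precise than it could be

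*Protocol article*

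**What the plan says.** The article fixes the primary outcome and its main test. Under Primary outcome: "The primary outcome is the number of blood donations made over 2 years". Under End-of-trial analyses: "Means will be compared between groups using a t-test, with subsidiary analyses of covariance adjusting for baseline characteristics". The adjusted analysis is therefore secondary in status.

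The section on randomisation describes a minimisation algorithm with a declared aim: "key prognostic characteristics are balanced across the trial arms at baseline (for example, new/repeat donor status, weight and age, as shown in Table 2"). The same section adds: "Randomisation was stratified by donation centre and gender". Table 2 splits age, weight and donor status into two categories each.

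Under Data analysis, Principles, men and women are analysed separately, so sex is respected. For outcomes measured at both time points, "analyses of the 2-year follow-up measures will be adjusted for the baseline measures". For the rest: "Other baseline characteristics (age, centre, BMI and weight, SF-36v2 physical and mental component scores, haemoglobin and ferritin) will be adjusted for in secondary analyses". That list contains centre, age and weight. It contains neither new/repeat status nor past donation rate.

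Baseline data collection states that the donor records retrieved include "previous donation and deferral history in the past 5 years". The key secondary outcome, the SF-36v2 physical component score (PCS), is adjusted for its baseline value in its main analysis.

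**The concern.** An analysis should normally reflect the way patients or donors were allocated. Stratification and minimisation remove part of the chance variation between arms. A two-sample t-test does not know this: its variance still contains the spread due to the balanced factors, so it overstates the uncertainty of the difference.

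The second issue is different in kind. A donor's past donation rate is the nearest available baseline counterpart of the primary outcome. It was not a balancing factor, except in so far as new/repeat status captures it. Leaving it out does not distort the standard error. It only leaves explainable variance in the residual.

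The plan also treats its two leading outcomes differently. PCS gets baseline adjustment in the main analysis, and donations do not, although the history is on file. Even the subsidiary adjusted analysis, as listed, would omit one minimisation factor. At stake are the width of the intervals and the sensitivity of the subgroup work, for which the trial was deliberately made large.

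**Working it through.** **Inputs from the article (Sample size; Table 4).** Control mean 1.6 donations/yr; SD 0.7/yr; target difference 5% × 1.6 = 0.08/yr; type I error 0.05 (taken as two-sided); 50,000 donors; 1:1:1 within sex; men 47% of the donor population.

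**Assumed inputs.** R², the share of outcome variance explained by centre, age, weight and donor status: 0.02 to 0.20. r, the correlation of past with 2-year donation rate: 0.4 to 0.6. The article gives neither.

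**The plan's own figure.** It states 80% power in subgroups of at least 5,000 donors. n per arm = 2 × (1.960 + 0.842)² × 0.7² / 0.08² = 1,202, or 3,606 over three arms. With 5,000 donors over three arms (1,667 each) power is 91.0%, so 80% is met as a lower bound. Over six sex-specific arms (833 each) it is 64.5%. Figure 2a is not available here, so I do not call the stated figure wrong. The calculation uses the full SD of 0.7, consistent with an unadjusted test.

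**Effect 1: balanced factors ignored.** If the factors are fully balanced, the true standard error is √(1 − R²) times the one the t-test reports. Actual size = 2 × [1 − Φ(1.96/√(1 − R²))].

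| R² (assumed) | true SE / t-test SE | actual size | coverage of 95% CI |
|---|---|---|---|
| 0.02 | 0.990 | 4.8% | 95.2% |
| 0.05 | 0.975 | 4.4% | 95.6% |
| 0.10 | 0.949 | 3.9% | 96.1% |
| 0.20 | 0.894 | 2.8% | 97.2% |

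**Effect 2: history ignored.** Residual variance is multiplied by 1 − r², that is 0.84, 0.75 or 0.64 at r = 0.4, 0.5 or 0.6: a reduction of 16%, 25% or 36%. The standard error is multiplied by 0.917, 0.866 or 0.800.

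**Simulation check.** 833 per arm, 25 centres × 8 cells, balance forced within cells, 2,000 runs. With design R² = 0.10 and an independent history term explaining 0.20:
- The mean t-test SE was 0.0343 against an empirical SE of about 0.0325.
- Rejection under the null was 3.4%.
- Power for 0.08/yr was 66% with the t-test, 70% adjusting for the design factors and 81% adding history.

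**Whole-sex comparisons.** Men: 50,000 × 0.47 / 3 = 7,833 per arm, SE = 0.7 × √(2/7,833) = 0.0112. Women: 50,000 × 0.53 / 3 = 8,833 per arm, SE 0.0105. Power for 0.08/yr exceeds 99.9% in both. For men the 95% half-width (1.96 × SE) is 0.022/yr unadjusted and 0.022 × 0.800 = 0.018/yr at r = 0.6.

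**Within-subgroup illustration.** For a 10% subgroup split by sex (833 per arm), power for 0.08/yr is 64.5% unadjusted and 72.1%, 76.8% or 83.0% at r = 0.4, 0.5 or 0.6. This is the contrast between two arms inside one subgroup. It is not the power of the planned interaction test. If the residual variance falls by the same proportion inside and outside the subgroup, the standard error of the interaction shrinks by the same factor √(1 − r²).

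**The case against.** The strongest reply is that the planned test is sound. It is unbiased, any error in its size is on the safe side, and it matches the unadjusted SD used for the sample size. Adjusted analyses are already planned and cover three of the four allocation factors. All of this stands.

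It also stands that the primary comparisons barely move: a half-width of 0.022/yr falling to 0.018/yr at best, against a target of 0.08/yr. At R² = 0.02 the size is practically nominal, and the formula assumes complete balance on every factor. Past donation was accrued under the standard intervals, and about 10% of donors are new and have none, so it is an imperfect baseline.

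Two stronger readings are tempting and should be resisted. A reader might infer that omitting donation history also makes the standard error too large. It does not, because history was not balanced by design; only efficiency is lost. A reader might also infer from the 64.5% that the t-test leaves the trial underpowered. That figure comes from splitting 5,000 donors by sex, which is a matter of sample size, and the article assesses subgroups by interaction tests whose model the t-test sentence does not specify.

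What does not stand is that this is merely detail left to an analysis plan. The article itself names the primary test and lists the adjustment covariates.

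**Conclusion.** The point holds as one of efficiency and of consistency with the allocation scheme, not of validity. The primary t-test is conservative to a degree that depends on an unstated R²: from almost nothing at 2% of variance to an actual size of 2.8% at 20%. Separately, leaving out past donation rate gives up a variance reduction of 16% to 36%, if r lies between 0.4 and 0.6. Neither range has a source in the article. The textual facts are certain; the size of the gain is not.

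The main conclusions for men and for women would not change. The benefit lies in narrower intervals and in more precise subgroup and interaction estimates. The change is worth making because it costs almost nothing and brings the primary outcome into line with the treatment of PCS.

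**What to change.** Within each sex, make the primary analysis a linear model of annualised donations on arm, centre, age category, weight category, new/repeat status and annualised donation rate before enrolment (0 for new donors, with the new-donor indicator in the model). Use the same covariates in the interaction models. Keep the unadjusted t-test as a sensitivity analysis. Add new/repeat status and past donation rate to the covariate list under Principles.

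The cost is a change of wording, to be made before the 2-year outcomes are analysed, and slightly more analysis work. The covariates are already collected. History brings no gain within the new-donor subgroup.

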**Methods/Design:**

INTERVAL is a randomised trial of whole blood donors enrolled from all 25 static centres of NHS Blood and Transplant. Recruitment of about 50,000 male and female donors started in June 2012 and was completed in June 2014. Men have been randomly assigned to standard 12-week versus 10-week versus 8-week inter-donation intervals, while women have been assigned to standard 16-week versus 14-week versus 12-week inter-donation intervals. Sex-specific comparisons will be made by intention-to-treat analysis of outcomes assessed after two years of intervention. The primary outcome is the number of blood donations made. A key secondary outcome is donor quality of life, assessed using the Short Form Health Survey. Additional secondary endpoints include the number of ‘deferrals’ due to low haemoglobin (and other factors), iron status, cognitive function, physical activity, and donor attitudes. A comprehensive health economic analysis will be undertaken.

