#### Other secondary outcomes

Other secondary outcomes, also to be assessed at 2 years, will include the following:i)The number of ‘deferrals’ of donors over the 2 years of the trial due to low haemoglobin levels and/or other factors (for example, clinical reasons, tattoos, piercings, and foreign travel).ii)Measures of iron status, including serum ferritin and reticulocyte haemoglobin.iii)Cognitive function tests of attention, executive function, intelligence, and episodic memory.iv)Physical activity measured by accelerometry.v)Cost effectiveness.vi)Donor attitudes assessed through questionnaire responses and interviews.

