#### Sample size calculations related to the outcomes

This trial has been powered on its primary endpoint (number of blood donations over 2 years) and key secondary endpoint (physical component quality of life score).

(1) *Number of blood donations:* As the men in this trial are assigned to 12-wk versus 10-wk versus 8-wk inter-donation intervals, the maximum number of donations possible over the 2-year trial duration are 8, 10, and 12 donations, respectively (that is, a 25% proportional increase in donation rates when comparing a 10-wk versus 12-wk frequency, or a 50% proportional increase when comparing a 8-wk versus 12-wk frequency). Women are assigned to 16-wk versus 14-wk versus 12-wk inter-donation intervals, corresponding to a maximum number of donations over 2 years of 6, 7, and 8 respectively. However, when considering the current nonattendance rates of donors, such maximal differences based on more frequent donation intervals are unlikely to be achieved in practice.

Hence, the power calculations are based on having 80% power to detect a more realistic 5% increase in the number of donations over two years. Such an increase would be of relevance to NHSBT since it would yield an additional 70,000 units of blood per year from the same donor base. Figure 2a shows that 50,000 trial participants will provide 80% power to detect ≥5% difference in donation rates/year in subgroups with a prevalence of ≥10% (at least 5,000 donors). The sample size calculation assumes type I error = 0.05 and mean donation rate = 1.6 times/yr in the standard donation frequency group (control), and between subject SD = 0.7 times/yr in each group.

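### The deferral outcome is defined as a number over 2 years but analysed as a proportion with no stated denominator; read per visit, that analysis removes the deferrals that come from extra visits

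*Protocol article*

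**What the plan says.** Under Other secondary outcomes, item (i) is a count: "The number of ‘deferrals’ of donors over the 2 years of the trial due to low haemoglobin levels and/or other factors". The abstract also describes it as a number: "Additional secondary endpoints include the number of ‘deferrals’ due to low haemoglobin (and other factors".

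Under End-of-trial analyses, after the methods for blood collected and for the SF-36v2 physical component score (PCS), the article says "Other secondary outcomes will be analysed similarly". It then gives deferrals a sentence of their own: "The proportion of deferrals will be analysed using logistic regression, allowing for potential over-dispersion between individuals". What the proportion is a proportion of is not stated, and no model for the number of deferrals is named.

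Three other places bear on the point. The Principles paragraph commits to intention-to-treat comparison of the randomised groups. The Background says haemoglobin is screened at every visit. The sample size section gives the ceiling on donations by arm: for men, "the maximum number of donations possible over the 2-year trial duration are 8, 10, and 12 donations, respectively"; for women, "corresponding to a maximum number of donations over 2 years of 6, 7, and 8 respectively".

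**The concern.** A number over a fixed period and a proportion are different quantities, and here the difference depends on the intervention. Allowing for extra variation between donors makes sense only when each donor contributes several yes/no results, so the natural reading is deferrals out of visits. The randomised interval is meant to increase visits. Dividing by visits therefore conditions on something the allocation changes, and the result is no longer a plain comparison of donors as randomised.

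The first objective is to raise supply without an unacceptable increase in iron deficiency or anaemia. The primary outcome is expressed per person. If deferrals are judged per visit, the gain is counted per donor while part of the cost is divided out. The Background also says that deferral may discourage later donation and raise collection costs. Both consequences follow from how many deferrals donors experience, not only from the risk at each visit.

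**Working it through.** **Inputs.** Maximum donations over 2 years: men 8, 10, 12; women 6, 7, 8 (sample size section). Control rate 1.6 donations a year and a realistic increase of 5% (same section). About 3% of donors fail the haemoglobin threshold at screening (Background). Two assumptions: the 3% is used as a constant risk per visit, and donations stand in for visits.

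**The plan's own figures.** Primary outcome section: "The number of blood donations up to (and not including) the 2-year anniversary date of recruitment will be counted". Taking 2 years as 104 weeks and counting multiples of the interval strictly before week 104 gives 8 (12-week), 10 (10-week), 12 (8-week), 6 (16-week) and 7 (14-week). Then 10/8 = 1.25 and 12/8 = 1.50. The stated maxima and the 25% and 50% increases are reproduced.

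**Formulas.** With v visits and constant risk p per visit:
- deferrals per donor = v × p, so the ratio between arms is v₂/v₁ whatever p is;
- per-visit odds ratio = [p/(1−p)] / [p/(1−p)] = 1.00 whatever p is;
- share ever deferred = 1 − (1−p)^v.

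**Results at p = 0.03.**

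| Comparison | Visits | Deferrals per donor | Ratio | Per-visit OR | Ever deferred | OR, ever deferred |
|---|---|---|---|---|---|---|
| Men, 12 v 8 weeks, maximum | 8 v 12 | 0.24 v 0.36 | 1.50 | 1.00 | 21.6% v 30.6% | 1.60 |
| Men, 12 v 10 weeks, maximum | 8 v 10 | 0.24 v 0.30 | 1.25 | 1.00 | 21.6% v 26.3% | 1.29 |
| Women, 16 v 12 weeks, maximum | 6 v 8 | 0.18 v 0.24 | 1.33 | 1.00 | 16.7% v 21.6% | 1.38 |
| Women, 16 v 14 weeks, maximum | 6 v 7 | 0.18 v 0.21 | 1.17 | 1.00 | 16.7% v 19.2% | 1.19 |
| Realistic increase | 3.2 v 3.36 | 0.096 v 0.101 | 1.05 | 1.00 | 9.3% v 9.7% | 1.05 |

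The last row uses 1.6 × 2 = 3.2 and 3.2 × 1.05 = 3.36. The assumed risk changes the level but not the ratio: for 8 v 12 visits, p = 0.01 gives 0.08 v 0.12 and p = 0.05 gives 0.40 v 0.60.

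**With variation between donors.** Beta-binomial data were simulated with mean risk 3% and 8,000 donors per arm (assumed, from about 50,000 over six groups), 1,000 runs per setting, with Pearson-scaled standard errors and a two-sided 5% test. For 8 v 12 visits and within-donor correlation 0.02, 0.05 and 0.10, the logistic analysis of deferrals out of visits gave an odds ratio of 1.00 and rejected in 4.4%, 5.1% and 5.1% of runs. A count analysis of the same data gave a ratio of 1.50 and rejected in 100%. Allowing for over-dispersion therefore does not restore the excess.

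**The direction can differ.** As a constructed example, 8 visits at 3.0% give 0.24 deferrals per donor and 12 visits at 2.5% give 0.30, which is 25% more. The per-visit odds ratio is (0.025/0.975)/(0.03/0.97) = 0.83.

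**The case against.** The denominator is inferred. If the proportion is the share of donors ever deferred, the excess does not vanish: at full attendance in men it is 21.6% v 30.6%, odds ratio 1.60. This stands. That reading still loses repeat deferrals, is not the number defined, and leaves the over-dispersion clause with nothing to do.

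The sentence that other secondary outcomes are handled in the same way could cover the number of deferrals by a comparison of means, with the logistic model as an addition. The text does not rule this out. But the deferral sentence follows immediately and is the only specific rule, so a reader would take it as the analysis. A statistical analysis plan may settle the matter. The point here is that the method named does not fit the outcome defined, not that detail is absent.

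A per-visit risk is a legitimate quantity. The Background describes harm through progressive loss of iron, which would raise the risk at each visit, and the logistic model would detect that. This stands too, and is why the per-visit analysis should be kept.

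A reader might go further and infer that the plan hides the trial's main safety signal. The document does not support that. Serum ferritin and reticulocyte haemoglobin are also secondary outcomes, and an independent committee reviews unblinded safety data at least every 6 months. A reader might also infer that low-haemoglobin deferrals are pooled with tattoos and travel. The outcome list names these reasons together but does not say that they are analysed as one.

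**Conclusion.** The mismatch between a defined number and an analysed proportion is in the text. On the natural per-visit reading, the part of any excess that comes from extra visits is removed. For any constant risk per visit the odds ratio is 1.00, while deferrals per donor rise in proportion to visits: about 5% at the protocol's realistic increase, and at most 50% in men and 33% in women at full attendance. The protocol itself says the maximal differences are unlikely to be reached, so 50% is a ceiling and not a forecast.

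The ratios do not depend on the 3%; the levels 0.24 and 0.36 do. How much donors pause or leave after a deferral is not given, so no figure here relies on it. It would be too strong to say that the planned analysis understates harm in general: it can miss a real excess per donor, but only the part that extra visits produce. The point concerns one of the lower-ranked secondary outcomes and leaves the primary and key secondary analyses untouched.

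**What to change.** - Main comparison: the number of low-haemoglobin deferrals per randomised donor over the fixed 2 years, by intention to treat within sex, using negative binomial regression or Poisson regression with robust standard errors, and no offset for attendance.
- Alongside it: the proportion of randomised donors ever deferred for low haemoglobin.
- Supportive: the per-visit proportion by over-dispersed logistic regression, with its denominator stated and a note that visits are affected by allocation.
- Deferrals for other reasons: reported separately.

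The cost is a change of wording and one more reported analysis. Attendance and deferrals are already retrieved from the donor database, so no new data are needed.
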